### Sample size {14}

To the authors' knowledge, there are no web-based training programs for transcultural competence in Germany. For this reason, a concise estimate of the expected effect size is difficult to provide. A systematic review from 2020 on the effectiveness of cultural competence with nine studies showed effect sizes from small (*d* = 0.10) to large (*d* = 2.11) [63]. An online intervention to increase transcultural competence in the USA revealed medium effect sizes for the dimension attitudes and skills and large effect sizes for the dimension knowledge [40]. Based on the mixed results, we opted for a medium effect size.

A calculation with the Shiny App [64] with an effect size of *Glass’ delta* = 0.5 showed that a linear mixed model 3 (measurement time: pre, post, follow-up 1) × 2 (groups: training group vs. waitlist control group) requires a sample number of *N* = 174 (*α* = 0.05, power = 0.95).

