**Methods:**

The training includes 6 modules, which are unlocked weekly. A total of *N* = 174 clinical psychologists are randomly assigned to two groups: the training group (TG) works through the complete training over 6 weeks, which includes a variety of practical exercises and self-reflections. In addition, participants receive weekly written feedback from a trained psychologist. The waitlist control group (WL) completes the training after the end of the waiting period (2 months after the end of the TG’s training). The primary outcome is transcultural competence. Secondary outcomes consist of experiences in treating people from other cultures (number of patients, satisfaction and experience of competence in treatment, etc.). Data will be collected before and after the training as well as 2 and 6 months after the end of the training.

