#### Relevant concomitant care permitted or prohibited during the trial {11d}

n/a: A non-clinical sample is studied and no clinical intervention is provided. Previously completed training in transcultural psychotherapy will be collected as a control variable.

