## Assignment of interventions: allocation

### Sequence generation {16a}

Participants will be randomly assigned to the training group or the waitlist control group. Blockwise randomization will be performed to make the groups equal in size until the target sample size is reached. The size of the blocks will remain hidden from the supervisors accompanying the training.

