## Statistical methods

### Statistical methods for primary and secondary outcomes {20a}

Outcomes will be evaluated using intention-to-treat (ITT) analysis. Group differences (group: training group vs. waitlist control group) in primary (transcultural competence; MCI and OnTracc) and secondary outcomes (experiences in treating people from other cultures) will be examined using piecewise linear mixed-effects models with repeated measures (time point: pre, post, follow-up 1). Likely will piecewise linear mixed-effects models be used to examine the longer-term effect of the training (including the four time points: pre, post, follow-up 1, and follow-up 2). The significance level will be set at *p* < .05.

Sociodemographic data will be listed by group condition and for the total group. Group comparisons will be examined at baseline to check for successful randomization. Categorical data are reported as *N* (%), continuous data as mean (SD).

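### The 174 participants said to be required for 95% power are also the number randomised, with no allowance for loss, and the inputs needed to check the 95% are not stated

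*Protocol article*

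**What the plan says.** Protocol article, Sample size {14}: a Shiny App calculation "with an effect size of *Glass’ delta* = 0.5" for a linear mixed model with three time points (pre, post, follow-up 1) and two groups "requires a sample number of *N* = 174 (*α* = 0.05, power = 0.95". The section gives no sidedness, within-person correlation, tested contrast or expected loss.

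Abstract, Methods: "174 clinical psychologists are randomly assigned to two groups". Sequence generation {16a} says that block randomisation will "make the groups equal in size until the target sample size is reached". The required number and the randomised number are therefore the same.

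Loss is foreseen elsewhere. Strategies to improve adherence {11c} defines when a silent participant counts as a dropout. Plans to promote participant retention {18b} sets out a series of reminders for questionnaires that are not returned.

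Statistical methods {20a} plans intention-to-treat piecewise mixed models over pre, post and follow-up 1. It sets a significance level of .05 without saying whether tests are one- or two-sided, and does not say how the baseline (t0) score enters the model.

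**The concern.** A sample size that is just enough for 95% power with complete data is not enough once anyone is lost, and this plan expects losses. The stated power is what readers will use to judge a null result: at 95%, a non-significant finding looks like fair evidence against an effect of 0.5, and at 85 to 90% it is weaker evidence.

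The figure cannot be checked either. For a repeated-measures model, the required number depends heavily on the pre-post correlation and on which contrast is tested. Without these and the sidedness, a reader cannot tell which 95% is being claimed.

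**Working it through.** **Inputs.** From Sample size {14}: N = 174, standardised effect 0.5 (SD = 1), α = 0.05, power 0.95. From Trial design {8}: 1:1 allocation, so 87 per arm. Assumed, because the document gives neither: loss of 10 to 30% and pre-post correlation ρ.

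**1. Reproducing 174.** For two independent groups at one time point, n per arm = 2(z_α + z_β)²/δ².

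- One-sided: 2(1.645 + 1.645)²/0.25 = 86.6, so 87 per arm, N = 174. The one-sided t version gives 176.
- Two-sided: 2(1.960 + 1.645)²/0.25 = 103.96, so 104 per arm, N = 208. The t version gives 105 per arm, N = 210. At 87 per arm, two-sided t power is 90.6%.

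**2. Two-sided mixed-model contrasts that also give about 174.** With 87 per arm, the variance that allows 95% two-sided power is 87 × 0.25/(2 × 3.605²) = 21.75/25.99 = 0.837.

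- Change from baseline, variance 2(1 − ρ): needs ρ of at least 0.58 (normal) or 0.59 (t).
- Baseline-adjusted, variance 1 − ρ²: needs ρ of at least 0.40 (normal) or 0.42 (t).

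So 174 fits several designs, and the text does not say which was used.

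**3. Effect of loss, taking 174 at face value.** Suppose 174 gives exactly 95% two-sided with complete data, and a fraction d contributes nothing after baseline. Power is then Φ(3.605·√(1 − d) − 1.960).

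| Loss d | 3.605·√(1 − d) | Power |
|---|---|---|
| 0 | 3.605 | 95.0% |
| 10% | 3.420 | 92.8% |
| 20% | 3.224 | 89.7% |
| 30% | 3.016 | 85.5% |

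If the 95% was one-sided, 20% and 30% loss give 90.3% and 86.6%. This step does not depend on how 174 was derived.

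**4. What the baseline score can recover.** Constraining the t0 means to be equal, or adjusting for t0, multiplies the standard error of an unconstrained change contrast by √[(1 − ρ²)/(2(1 − ρ))] = √[(1 + ρ)/2]. At ρ = 0.5 this is √0.75 = 0.87. Two-sided t power with 87 per arm randomised and ρ = 0.5:

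| Loss | Change, unconstrained | Baseline-constrained or adjusted |
|---|---|---|
| 20% | 83.4% | about 92% |
| 30% | 78.1% | about 89% |

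At ρ = 0.5 the change variance 2(1 − ρ) equals 1, which is why the unconstrained column matches a simple two-sample test.

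**The case against.** **Was the calculation really a one-sided two-sample one?** A reader might infer this from the exact match at 87 per arm. The document does not support it. It names a 3 × 2 mixed model run in an app whose inputs are not shown, and two-sided contrasts at moderate correlations give about the same number. The match is a coincidence worth explaining, not a demonstrated error.

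**Does the planned analysis deliver only about 78 to 90%?** This is also tempting, and it is not established. That range mixes sidedness and rests on assumed loss and, for a change contrast, on ρ near 0.5. Over ρ from 0.3 to 0.8, two-sided power of longitudinal contrasts of the planned type at 20 to 30% loss runs from about 65% to above 99%. The high values do not rescue the stated figure, however. At ρ = 0.7 a change contrast needs only 126 in total for 95%, so 174 would not be the number required.

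**Loss may cost less than shown.** This stands. All randomised participants enter the analysis, and a mixed model uses those with some follow-up data. The losses above apply to people with no post-baseline data.

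**An article condenses the full protocol.** This has little force here. The section on access to the protocol {31c} says the article is the complete protocol, and the point concerns a stated figure rather than an omitted detail.

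**The baseline constraint is a modelling preference.** This stands in part. The analysis section does not say that the model is unconstrained, and the parameterisation may sit in an analysis plan. The constraint is a cheap gain in precision, not the correction of an error.

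**Conclusion.** The concern holds in a limited form. The number required for 95% power is the number randomised, so the stated power is reached only with no loss, which the plan does not itself expect. If 174 is exactly sufficient for a two-sided test with complete data, the shortfall is about 2 points at 10% full loss, 5 at 20% and 9.5 at 30%. The loss rates are assumptions, and the shortfall is smaller where participants give partial follow-up.

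Separately, the 95% cannot be verified without the sidedness, correlation and contrast. An arithmetic error in the 174 is not shown. The trial remains reasonably powered in many plausible settings. What needs correcting is the claim, and it should be corrected before results are read against it.

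**What to change.** (a) In Sample size {14}, restate the power for 174 randomised. Give a two-sided α, the assumed within-person correlation, the contrast tested, the expected loss at post and follow-up 1, and the power that results. Enrolment need not rise.

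(b) In Statistical methods {20a}, state that the t0 mean is constrained to be common to both arms, or that the model adjusts for the t0 score. That score is already collected before randomisation. Base the power in (a) on this same model.

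The cost is one rewritten paragraph, one model term and probably a less favourable stated power.

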### Recruitment {15}

Recruitment takes place via websites (e.g., state chamber of clinical psychologists), mailing lists (e.g., clinical psychologists, training institutes), advertisements (e.g., in German journals with a strong focus on therapeutic practice), and social media (therapist groups on Facebook or Instagram). Through a link, participants can obtain further information and access the study.

## Assignment of interventions: allocation

### Sequence generation {16a}

Participants will be randomly assigned to the training group or the waitlist control group. Blockwise randomization will be performed to make the groups equal in size until the target sample size is reached. The size of the blocks will remain hidden from the supervisors accompanying the training.

### Concealment mechanism {16b}

Implementation of the allocation sequence is allowed by Microsoft Excel [65]. The program randomly divides participants into evenly sized groups.

### Implementation {16c}

The randomization is performed by a research assistant who is not involved in the research project or in the training support. The research team of this study subsequently informs the participants of their condition by email.

## Assignment of interventions: blinding

### Who will be blinded {17a}

Due to the trial design, neither the participants nor the researchers will be blinded.

### Procedure for unblinding if needed {17b}

n/a. Since there is no blinding, no procedure for unblinding is required.

## Data collection and management

### Plans for assessment and collection of outcomes {18a}

All data will be collected online on the Unipark survey platform via participant self-report (https://www.unipark.com). The primary (transcultural competence) and secondary outcomes (experiences in treating patients with diverse cultural backgrounds) will be collected at each time point of measurement (pre, post, follow-up 1, follow-up 2). Control variables (sociodemographic information and therapeutic practice) will be assessed at baseline only. After training, satisfaction with the training (e.g., scope, practicability, formal design) will be assessed. For an overview of which questionnaires are applied at which time point, please refer to Fig. 1. For detailed information regarding the questionnaires, see {12}.

### Plans to promote participant retention and complete follow-up {18b}

Participant retention is promoted through weekly contact with a supervisor. For the follow-up surveys, participants are contacted by email. If the questionnaires are not completed within seven days, a reminder email will follow. If the questionnaire is still not answered, another e-mail will follow within a week. After 4 weeks, a last reminder to fill in the questionnaire follows. The emails emphasize the importance of completion in order to improve training and, in the long term, the availability of qualified training. At the same time, reference is made to the continuing education credit that participants receive after completing the final questionnaires. As all questionnaires can be answered online, participants can fill in the questionnaires flexibly and from any place. No further promotional measures will be taken to increase participation.

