#### Criteria for discontinuing or modifying allocated interventions {11b}

Due to the non-clinical sample, no criteria have been set to discontinue or modify the training. Participants can stop working with the training at any time, without providing an explanation There are no disadvantages from withdrawal, except that in the case of discontinuation, the participants cannot receive the certificate of attendance (i.e., continuing education credits).

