#### Strategies to improve adherence to interventions {11c}

Participants are encouraged to attend the training on a weekly basis. At the end of each module, the program suggests participants to plan a timeframe to complete the next module within a week. An online calendar supports this intention. Adherence is further supported by the feedback of a supervisor, who communicates with the participants at least once a week.

If the module has not been worked on after 5 days, the supervisor sends a reminder to encourage the participant to continue. The participant is also asked if and how the supervisor can support them to continue the training. If the participant still has not continued the training 1 week later, an additional reminder email follows. If neither the training is worked on nor are the emails answered for 3 weeks, the participant receives a last e-mail where he or she is asked whether there is still interest in participation. The e-mail also contains the information that the participation will be deleted if neither there is a reply to the e-mail nor the module is processed within the next 7 days. The participant is then considered to have dropped out of the study.

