#### Provisions for post-trial care {30}

n/a: There is no anticipated harm and compensation for trial participation apart from a certificate of attendance. For this reason, there will be no need to provide post-trial care. Nevertheless, participants can reach out to the study management via email or telephone at any time if needed.

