### Methods in analysis to handle protocol non-adherence and any statistical methods to handle missing data {20c}

The data are analyzed according to the intention-to-treat principles, and data of all individuals randomized in this trial will be entered in our analyses. The handling of missing data is reported in tables and results.

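### Trainees who stop forfeit the only material reward and can be classed as out of the study, which leaves the all-randomised comparison exposed at the post and 2-month visits

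*Protocol article*

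**What the plan says.** All references are to the protocol article.

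- **Reward.** Section {30} says: "There is no anticipated harm and compensation for trial participation apart from a certificate of attendance". Section {18b} says that in the e-mails "reference is made to the continuing education credit that participants receive after completing the final questionnaires", and adds: "No further promotional measures will be taken to increase participation". It does not define which questionnaires are the final ones.
- **Forfeit.** Section {11b} says that "in the case of discontinuation, the participants cannot receive the certificate of attendance (i.e., continuing education credits").
- **Status of inactive trainees.** Under section {11c}, a trainee who neither works on the modules nor answers e-mails for 3 weeks gets a last e-mail with a 7-day limit. If nothing happens: "The participant is then considered to have dropped out of the study".
- **Other retention measures.** Section {18b} also has: "Participant retention is promoted through weekly contact with a supervisor". It adds three timed reminders for unanswered questionnaires, an appeal to the importance of answering, and flexible online completion.
- **Timing by arm.** Under section {13}, the waitlist starts training only after its own 2-month assessment.
- **Analysis.** Section {20a} plans an intention-to-treat piecewise linear mixed model over pre, post and follow-up 1. Section {20c} undertakes to include everyone randomised and says of missing data: "The handling of missing data is reported in tables and results".

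**The concern.** An intention-to-treat estimate needs outcomes from people who gave up the training as well as from those who finished it. Here the rules on reward and on dropout both turn on training activity. A trainee who stops loses the one material reason to answer, and the reminders then cite a credit that this person can no longer earn. A trainee who falls silent is moved out of the study altogether, and no section says that such people are still sent the post and 2-month questionnaires.

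Before the 2-month visit, nobody on the waitlist can have stopped the training, so neither rule can remove a waitlist member from follow-up in this way. Any resulting loss is therefore confined to one arm and tied to how much training was received. A mixed model keeps a person who has only a baseline value, but it estimates the post-baseline means from those who answered. The result could be labelled an effect in all randomised while describing mainly those who stayed. Section {31a} makes wider release of the training depend on success, so the size of the effect matters.

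**Working it through.** **1. The plan's own figure.** Section {14} gives N = 174 for a Glass' delta of 0.5, α = 0.05 and power 0.95. As a simple comparison of two means, n per arm = 2(z_α + z_β)²/δ².

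- One-sided: 2 × (1.645 + 1.645)²/0.25 = 86.6, so 87 per arm and N = 174.
- Two-sided: 2 × (1.960 + 1.645)²/0.25 = 104.0, so 104 per arm and N = 208. A two-sided test also reaches 174 if a baseline correlation of about 0.40 is assumed (variance factor 1 − ρ²).

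The figure can be reproduced and is not shown to be wrong. It supplies the 0.5 SD gain and the 87 per arm used below. Section {14} mentions no dropout rate and no inflation for dropout.

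**2. Can the dropout rule act before the randomised visits?** Counted from the start of inactivity, section {11c} takes 3 weeks + 7 days = 4 weeks. The course lasts 6 weeks. A trainee who falls silent early can be classed as dropped out before the post assessment.

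**3. Effect in all randomised.** Let d be the share of the training arm who stop and do not answer, and g the fraction of the stayers' gain that they keep. Both are assumptions, since the protocol gives neither.

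Effect in all randomised = 0.5 × [(1 − d) + d × g]

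Overstatement = 0.5 ÷ that effect − 1, if the model returns the stayers' 0.5.

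| d | g | Effect in all randomised | Overstatement |
|---|---|---|---|
| 20% | 0 | 0.5 × 0.80 = 0.40 | 0.5/0.40 − 1 = 25% |
| 30% | 0 | 0.5 × 0.70 = 0.35 | 0.5/0.35 − 1 = 43% |
| 20% | 0.5 | 0.5 × 0.90 = 0.45 | 0.5/0.45 − 1 = 11% |
| 30% | 0.5 | 0.5 × 0.85 = 0.425 | 0.5/0.425 − 1 = 18% |

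Over a wider range with g = 0, the overstatement is 11% at d = 10% and 67% at d = 40%. With g = 0.5 it is 5% and 25%.

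**4. Does the mixed model return the stayers' gain?** This was checked by simulating a random-intercept piecewise model with three visits, 87 per arm, correlation 0.5, g = 0, stopping unrelated to baseline, and 150 runs per setting.

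| d | Stoppers answer at baseline only (post / 2-month) | Everyone followed (post / 2-month) |
|---|---|---|
| 20% | 0.51 / 0.50 | 0.41 / 0.40 |
| 30% | 0.51 / 0.50 | 0.36 / 0.36 |

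The simulation standard error is about 0.014 for the baseline-only columns. The model credits silent stoppers with the stayers' gain, and following everyone removes the error. This confirms the mechanism. It is not evidence about how many trainees will stop or how much they will gain.

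**The case against.** The strongest case on the other side has five parts.

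- **Stoppers still have reasons to answer.** A reader might infer that they have none. Section {18b} does not support that: there are three reminders, an appeal to the value of answering, and easy online access. What stands is that stoppers have no material reward, and that it is unclear whether those classed as dropped out still receive the reminders.
- **The post visit may be rewarded.** A reader might infer that nothing rewards the two randomised visits. The term *final questionnaires* is undefined. If it means the end-of-training questionnaires, trainees who finish are rewarded at post. Waitlist members also have the training ahead of them as an inducement. On either reading, those who stop earn nothing, so the difference between stoppers and stayers remains.
- **The waitlist may lose more.** A reader might infer that missing data will concentrate in the training arm. That is plausible but not shown. Trainees have weekly supervisor contact and offers of help, while no such contact is described for people waiting, and the limitations section itself raises dropout from waitlists. What is fixed is that loss through these two rules can arise only in the training arm.
- **Missing-data methods belong in an analysis plan.** Agreed: leaving the method open in {20c} is not an error. But no analysis plan can recover outcomes that the follow-up rules allow to go uncollected.
- **Withholding an attendance certificate from non-attenders is normal.** Also agreed. The problem is not the certificate itself. It is that nothing separate supports follow-up of those who stop, and that {11c} treats stopping as leaving the study.

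**Conclusion.** The point holds in this form. The rules in {11b}, {11c} and {18b} work against the promise in {20c} to analyse everyone randomised, and before the 2-month visit they can do so in the training arm only.

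The direction of the bias is conditional. The estimate moves towards the completers' effect if stoppers fail to answer and gain less than stayers. The bias shrinks if stoppers answer at post and miss only the 2-month visit, if many non-responders had in fact finished most modules, or if waitlist loss is similar in kind.

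The overstatements of 25–43% and 11–18% rest on an assumed 20–30% loss and on assumed gains of none and half. They should not be read as a forecast. The trial stays interpretable, but its intention-to-treat claim is not protected as the plan stands.

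**What to change.** **(a) Follow-up rules.**

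- State in {11c} and {18b} that stopping the training is not leaving the study. Every randomised participant who has not withdrawn consent is sent the post and 2-month questionnaires and the same reminders, whatever their training status.
- Word the reminders so that they do not rely on a credit that stoppers cannot earn.
- Define *final questionnaires*. For those who finish the training, make the credit depend on the post and 2-month questionnaires as well.

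**(b) One sensitivity analysis.** Beside the primary estimate, report a reference-based multiple imputation in which training-arm members without post or 2-month data follow the waitlist trajectory. In the illustration above this corresponds to g = 0, that is 0.40 at 20% loss and 0.35 at 30%.

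**Cost.** A protocol amendment is needed while recruitment is under way, and section {25} requires ethics approval for important changes. Because the training is accredited, the team should check whether the certificate rule can be changed without the chamber's agreement. The analysis is a small addition, and its estimate may be less favourable than the headline one.
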